# Cost-effectiveness of massed versus spaced trauma-focused treatment as first-line treatment for post-traumatic stress disorder in adults with multiple trauma exposure: protocol for a single-blind non-inferiority randomised controlled trial

**DOI:** 10.1136/bmjopen-2025-102530

**Published:** 2025-05-23

**Keywords:** Randomized Controlled Trial, Adult psychiatry, Psychosocial Intervention, Psychological Stress

## Abstract

**ABSTRACT:**

**Introduction:**

Post-traumatic stress disorder (PTSD) is a serious disorder that burdens individuals and society. The current standard of first-line treatment for PTSD is spaced trauma-focused treatment (S-TFT), involving weekly sessions. While effective, S-TFT may take relatively long to complete, especially in patients exposed to multiple potentially traumatic events (PTEs). Massed trauma-focused treatment (M-TFT), involving increased session frequency, potentially results in faster symptom reduction and restoration of quality of life, as well as in a reduction of societal costs. However, M-TFT is not recommended as first-line treatment. This paper describes the research protocol of a single-blind, multicentre randomised controlled trial (RCT) aimed at investigating: (1) the clinical and cost-effectiveness of M-TFT versus S-TFT in employed, multiply traumatised patients who seek first-line treatment for PTSD and (2) predictive and moderating factors related to treatment response.

**Methods and analysis:**

186 participants are recruited from five centres and will be included if they are ≥18 years old, meet criteria for a Diagnostic and Statistical Manual of Mental Disorders Fifth Edition PTSD diagnosis based on ≥two PTEs, seek treatment for the first time and are employed. Patients with specified comorbid disorders and insufficient Dutch language proficiency are excluded. Participants are randomised to 800 min of either M-TFT or S-TFT. M-TFT consists of two once-weekly preparatory sessions, 10 twice-daily sessions of prolonged exposure, eye movement desensitisation and reprocessing therapy for 2 weeks and two once-weekly closing sessions. S-TFT consists of weekly sessions of one of five evidence-based treatment interventions. Outcomes are assessed at baseline and at 7 weeks, 17 weeks, 6 months and 9 months after baseline. Primary outcomes are clinical effectiveness in terms of PTSD symptom severity and cost-effectiveness based on quality of life measures and societal costs. Data will be analysed with linear mixed models.

**Ethics and dissemination:**

This study protocol was approved by the Medical Ethics Review Board of the Amsterdam University Medical Center (NL86057.018.24). Participants will provide informed consent before enrolment in the trial. Results will be published in peer-reviewed journals and will be released to clinicians, patient groups and the general community.

**Trial registration number:**

This protocol is registered at Overview of Medical Research in the Netherlands (OMON; trial register number 56960) and ClinicalTrials.gov (NCT06700590).

STRENGTHS AND LIMITATIONS OF THIS STUDYWith the inclusion of 186 participants, this randomised controlled trial (RCT) will be well-powered to establish the non-inferiority of massed trauma-focused treatment (M-TFT) compared with spaced-TFT (S-TFT).The current RCT will be conducted at five centres throughout the Netherlands, which will enrol patients with a variety of trauma backgrounds, increasing the generalisability of the findings.Assessments will be performed at five time points from baseline to 9-month follow-up, which allows for accurate investigation of the (cost-)effectiveness of the treatments over time.Elements of pragmatic, real world RCTs are present in the S-TFT condition in which multiple types of evidence-based trauma treatment are allowed, enabling a more representative comparison of M-TFT to standard clinical care.A potential limitation concerns differences between the M-TFT condition and the S-TFT condition in terms of therapist rotation, supervision frequency and the alternation of therapeutic elements.

## Introduction

 Post-traumatic stress disorder (PTSD) is a severe psychiatric disorder characterised by intrusive memories, avoidance, negative alterations in cognition and mood and hyperarousal.^1^ It is associated with psychiatric and somatic comorbidity such as depression and chronic pain, reduced quality of life and increased societal costs.^2^,^4^ Several treatment interventions have demonstrated large effect sizes for PTSD and comorbid symptom reduction^5^,^7^ and consequently are recommended as treatments of choice for PTSD. These include eye movement desensitisation and reprocessing (EMDR) therapy and various forms of trauma-focused cognitive-behavioural therapy (e.g., prolonged exposure (PE), cognitive (processing) therapy, brief eclectic psychotherapy for PTSD (BEPP), narrative exposure therapy (NET) and imagery rescripting (ImRs)).

With regards to session amount and frequency, treatment guidelines for PTSD advise a minimum of eight sessions of evidence-based treatments, that are delivered at least once a week.^8 9^ Although effective, the standard frequency of spaced (i.e., weekly) trauma-focused treatment (S-TFT) has several drawbacks. Treatment completion typically takes 8–12 weeks, with a longer treatment duration for those who have been exposed to multiple or prolonged traumatic events.^9^ Pooled drop-out rates are relatively high, around 16%,^7^ and are related to (among other factors) treatment dissatisfaction and concerns or constraints interfering with therapy, such as irregular working hours.^10 11^

In massed trauma-focused treatment (M-TFT), time between sessions is strongly reduced, with frequencies ranging from three sessions per week to multiple sessions per day. With less potential for therapy disruption, M-TFT might benefit patients with outside constraints interfering with therapy.^11 12^ Also, M-TFT might enable those with avoidant coping to more easily complete treatment. Randomised controlled trials (RCTs) found that M-TFT leads to faster symptom reduction while maintaining effectiveness in the short term and long term and has drop-out rates either comparable with or lower than spaced treatments.^13^,^16^

Even though M-TFT has potential benefits over S-TFT, the current Dutch treatment guidelines for PTSD only recommend M-TFT after patients have shown an insufficient treatment response to two evidence-based interventions of S-TFT.^8^ Consequently, treatment may become unnecessarily prolonged and cost-ineffective, especially in multiply traumatised patients. A previous study comparing the cost-effectiveness of M-TFT and S-TFT in patients with childhood abuse-related PTSD^17^ found a small but significant difference of 0.027 in quality-adjusted life years (QALYs) in favour of massed treatment. As PTSD results in an average of 15.2 additional days of absenteeism,^3^ the cost-effectiveness of M-TFT might be higher in employed patients due to a faster reduction in absenteeism. Conducting M-TFT as a first-line treatment for PTSD might therefore reduce societal costs related to PTSD.

This paper describes the study protocol for a multicentre, parallel (1:1), single blinded, RCT of M-TFT versus S-TFT as First-Line Intervention for PTSD - Intensive Treatment, using the acronym FLIP-IT. The primary aim of the trial is twofold: (1) to investigate whether M-TFT is non-inferior to S-TFT in reducing PTSD symptoms in employed patients who have been exposed to multiple potentially traumatic events (PTEs) and who seek first-line treatment for PTSD and (2) to investigate the clinical and cost-effectiveness of M-TFT versus S-TFT. Following the literature, we hypothesise that while long-term effectiveness is comparable to S-TFT, M-TFT’s higher session frequency leads to faster symptom relief,^13^,^16^ enhancing patients’ quality of life and leading to lower societal costs.^17^

Secondary aims concern investigating differential effects on drop-out and identifying predictors and moderators of treatment outcome. We hypothesise that M-TFT has lower drop-out than S-TFT. In line with previous research, we also hypothesise that comorbid disorders, dissociation, experiential avoidance, verbal memory, trauma background and cortisol levels are negative predictors of treatment outcome in both conditions, while social support is a positive predictor.^2^ Last, through qualitative analysis, we aim to understand who may benefit most from M-TFT versus S-TFT and how to improve its application.

## Methods and analysis

### Participants

For study eligibility, participants must meet the following inclusion criteria: (1) be 18 years or older; (2) have a PTSD diagnosis according to the Diagnostic and Statistical Manual of Mental Disorders Fifth Edition (DSM-5) as assessed with the Clinician-Administered PTSD Scale – Revised (CAPS-5-R; see below); (3) have a history of exposure to two or more PTEs; (4) have attended less than eight TFT sessions; (5) be employed (working or on sick leave for <2 years). Patients who meet any of the following criteria will be excluded from participation: (1) have a current psychotic disorder, severe alcohol or substance use disorder or high suicidal intent with a concrete suicide plan as assessed through the Mini International Neuropsychiatric Interview – Short (MINI-S, see below) for DSM-5 or severe aggressive behaviour that poses a danger to others (assessed through self-report of aggressive behaviour towards other people in the last month); (2) have an insufficient command of the Dutch language to complete the assessments. The inclusion of 186 participants started on 18 November 2024 and is planned to last until July 2027.

### Study design and procedures

#### M-TFT protocol

The M-TFT protocol is a comprehensive treatment approach designed to address PTSD through a structured series of sessions. Participants engage in two preparatory sessions once per week, lasting 50 min each, focusing on psychoeducation and case conceptualisation. In the third week, the core treatment starts, consisting of 5 days of M-TFT delivered over 1 week or 2 weeks. Each M-TFT day features a 60-minute PE therapy session, a break and a 60 min EMDR session. The sequencing of PE followed by EMDR has been demonstrated to be more effective than the reverse order.^18^ Two 50-minute closing sessions, one in week 5 and one in week 6, consist of summarising learnt information and preventing relapse. To enhance feasibility, therapist rotation may be incorporated into the treatment plan, which has been found to have no negative effects on the therapeutic relationship.^19^ The total treatment duration for M-TFT is 800 min over 5–6 weeks.

#### S-TFT protocol

The S-TFT protocol comprises either 12 weekly 60-minute sessions plus a last 80-minute session (13 total sessions) or 16 weekly 50-minute sessions, both amounting to a total treatment duration of 800 min. This variable session structure was chosen in order to align with the existing financial reimbursement structures of the participating treatment sites. The S-TFT protocol consists of evidence-based first-line treatment interventions according to the Dutch treatment guideline for PTSD,^8^ which include PE, EMDR therapy, BEPP, NET and ImRs. Although different trauma-focused interventions are applied, they share core elements, including psychoeducation, imaginal exposure, emotional processing, cognitive restructuring and/or meaning-making.^20^ This condition therefore strongly resembles standard clinical care in the Netherlands. The S-TFT protocol does not include therapist rotation.

Both treatment conditions will be conducted face to face at five outpatient treatment centres specialising in psychotrauma in the Netherlands: ARQ Centrum’45, ARQ IVP, Psy-Zo!, Psychotraumacentrum Haarlem and the Military Mental Health Care.

We increase treatment fidelity through several measures. Study therapists must be licensed psychologists or be supervised by one. For all treatment interventions, certified and specific training in each modality is required. Also, therapists are required to follow a mandatory 2.5-day certified training on massed trauma treatment, covering the latest developments in the treatment interventions used in the study. Supervision with a frequency of once every 3 weeks for M-TFT and once every 6 weeks for S-TFT is provided to address treatment progress and problems. Furthermore, audio recordings of the therapy sessions will be made, and a random sample of recordings will be checked for treatment fidelity using checklists tailored to the specific treatment.

#### Medication use

Patients are requested to keep their medication type and dosage stable during the study. At the beginning of each treatment day, therapists will inquire about medication type or dosage changes. Adherence to the instruction will also be monitored at all post-assessments and changes will be recorded.

No concomitant TFT during the study is allowed. If patients decide to drop out of the study, they can finish their treatment.

### Measures

Assessments will be conducted at baseline (T0), after massed treatment is finished (7 weeks; T1), after spaced treatment is finished (17 weeks; T2) and at 6 months and 9 months after baseline (T3 and T4). Assessment points are the same for both groups. Table 1 provides an overview of all measures and treatment duration at each timepoint. Primary outcomes consist of PTSD symptom severity and cost-effectiveness (based on quality of life and inventory of societal costs).

**Table 1 T1:** Assessments at each time point

TimepointsAssessments	T00 weeks	T17 weeks(end M-TFT)	T217 weeks(end S-TFT)	T36 months	T49 months
MINI-S	X				
LEC-5	X				
CAPS-5-R	X	X	X	X	X
TIC-P	X		X	X	X
VLGT	X		X		
ITQ	X	X	X	X	X
ACE-IQ	X				
MHQoL	X	X	X	X	X
EQ-5D-5L	X	X	X	X	X
HADS	X	X	X	X	X
MIOS	X	X	X	X	X
AAQ-II	X	X	X	X	X
PID-5	X			X	
DSS-4	X	X	X	X	X
CEQ	X				
CSS	X			X	
Cortisol	X				
CSQ-8 + VAS		X (massed)	X (spaced)		
Treatment format evaluation		X (massed)	X (spaced)		

AAQ-II, Acceptance and Action Questionnaire II; ACE-IQ, Adverse Childhood Experience International Questionnaire for adults; CAPS-5-R, Clinician Administered PTSD Scale for DSM-5 – Revised; CEQ, Credibility and Expectancy Questionnaire; CSQ-8, Client Satisfaction Questionnaire; CSS, Crisis Social Support Scale; DSS-4, Dissociative Symptoms Scale 4; EQ-5D-5L, EuroQol 5 Dimensions scale; HADS, Hospital Anxiety and Depression Scale; ITQ, International Trauma Questionnaire; LEC-5, Life Events Checklist for DSM-5; MHQoL, Mental Health Quality of Life questionnaire; MINI-S, Mini International Neuropsychiatric Interview – Simplified for DSM-5; MIOS, Moral Injury Outcome Scale; PID-5, Personality Inventory for DSM-5-Brief Form-Adult; TIC-P, Treatment Inventory of Costs in Patients with psychiatric disorders; VAS, Visual Analogue Scale; VLGT, Verbal Learning and Memory Test.

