#### Treatment evaluation

To gain a better understanding of when to implement massed treatment and how to improve its application, we will carry out a qualitative assessment of participants’ experience, consisting of two parts. The first part entails open-ended questions to assess satisfaction with the therapy format and its execution. Participants will answer the questions in table 2 as part of a self-report questionnaire after their treatment has ended (at T1 for the M-TFT condition and at T2 for the S-TFT condition).

**Table 2 T2:** Topic list used in treatment evaluation

Questionnaire after treatment completion	Focus group
What was your experience of the treatment?	What was your experience of the treatment?
What do you see as the advantages of spaced therapy?	Which type (massed or spaced) of therapy do you prefer? Why?
What do you see as the disadvantages of spaced therapy?	What would be the optimal frequency of therapy for you? Why?
What do you see as the advantages of massed therapy?	What factors aided or hindered your treatment?
What do you see as the disadvantages of massed therapy?	What changes can we make to improve the quality of treatment?
For you specifically, what do you think would be the biggest difference between doing massed and spaced therapy?	On which aspects would you have liked to receive more help? On which ones less?
After the treatment, what treatment type would have been a better fit for you? Why do you think that is?	What were some things covered in therapy that were not valuable for you? What were some things covered in therapy that were particularly valuable to you?
What would have been the optimal frequency of treatment for you? Why?	Is there anything else you would like to say about the therapy and how it was given?
Is there anything else you would like to say about the therapy and how it was given?	
*For massed specifically:* what was your experience with therapy rotation?	
*For massed specifically:* what did you think about the order (i.e., PE and then EMDR) of treatments? Would you rather have had it the other way round? Why (not)?	

Note: the interview questions will be asked at T1 for M-TFT and at T2 for S-TFT. Focus groups will be held at the end of the study.

EMDR, eye movement desensitisation and reprocessing; M-TFT, massed trauma-focused treatment ; PE, prolonged exposure; S-TFT, spaced trauma-focused treatment ; T1, 7 weeks after baseline; T2, 17 weeks after baseline.

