### Study procedures

The baseline measurement will be split to reduce the burden on participants. One part of the baseline measurement will be conducted immediately after obtaining informed consent (i.e., general questions, inclusion and exclusion criteria, MINI-S, LEC-5, CAPS-5-R, VLGT and hair sample; see table 1). The self-report questionnaires of the baseline measurement are filled out separately, at home, with a research team member present online for questions and completeness of the data.

Consequently, participants are randomly assigned to either M-TFT or S-TFT in a parallel design. The random assignment is carried out on a 1:1 basis using Castor EDC, which incorporates blocked randomisation of 2, 4 and 6, stratified by location. A research associate employed by the sponsor who is not otherwise involved in the study will assign patients to their respective treatment.

Informed consent and the first part of the baseline measurement will take place at a participating centre; all other assessments will take place in online meetings (T1–T4). Assessments will be conducted by psychologists and master’s-level psychology students who have received training in all assessment procedures and instruments. Outcome assessors will administer all clinician-rated instruments blind to treatment conditions. To enhance participant retention, participants will receive €25 if they complete the measurement at T4.

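### T1 (week 7) and T2 (week 17) are counted from baseline but treated as the end of M-TFT and S-TFT; with 16-session S-TFT or six-week M-TFT they can fall before the last session

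*Protocol article*

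**What the plan says.** All places are in the protocol article.

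- **Measures and Table 1.** Both arms follow one calendar. T1 at 7 weeks is described as the point after massed treatment. T2 is described as "after spaced treatment is finished (17 weeks; T2". The Table 1 column headings repeat these labels as the end of M-TFT and of S-TFT. The CSQ-8 + VAS and the treatment format evaluation appear once per patient: at T1 for massed, at T2 for spaced.
- **Treatment evaluation.** The evaluation questions are to be answered "after their treatment has ended (at T1 for the M-TFT condition and at T2 for the S-TFT condition". The note to Table 2 fixes the anchor: "T2, 17 weeks after baseline".
- **S-TFT protocol.** The spaced course is "either 12 weekly 60-minute sessions plus a last 80-minute session (13 total sessions) or 16 weekly 50-minute sessions". On the choice between the two: "This variable session structure was chosen in order to align with the existing financial reimbursement structures of the participating treatment sites".
- **M-TFT protocol.** The massed course takes 5 to 6 weeks, with closing sessions in weeks 5 and 6.
- **Study procedures.** Baseline has a part on site and a separate self-report part at home. Then: "Consequently, participants are randomly assigned to either M-TFT or S-TFT in a parallel design".
- **Clinical effectiveness.** The non-inferiority decision is taken at 9 months.

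**The concern.** A visit fixed on the calendar from baseline is equated with a treatment event whose date depends on when the first session takes place and how many weeks are missed. Where the course nearly fills the interval, the visit can come before the last session.

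Two things are at stake. First, the satisfaction scale and the format evaluation are given once and ask patients to look back on a finished treatment. If a patient is still in treatment, no later administration corrects the early answer. Second, labelling T2 as the end of S-TFT invites readers to take the week-17 scores (CAPS-5-R, HADS, quality of life) as post-treatment results in both arms. How far that is true differs by arm and, within S-TFT, by the session format of the site.

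**Working it through.** **Inputs from the article.** T1 is at week 7 and T2 at week 17, both from baseline (Measures; notes to Table 2). S-TFT has 13 or 16 weekly sessions (S-TFT protocol). M-TFT lasts 5 or 6 weeks (M-TFT protocol).

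**The article's own totals.** S-TFT: 12 × 60 + 80 = 800 min and 16 × 50 = 800 min. M-TFT: 2 × 50 + 5 × 120 + 2 × 50 = 800 min. All agree with the stated 800 min, so the session counts can be used as given.

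**Spare weeks with the first session in week 1** (visit week minus weekly slots needed):

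- S-TFT, 16 sessions: 17 − 16 = 1
- S-TFT, 13 sessions: 17 − 13 = 4
- M-TFT at T1: 7 − 6 = 1 (six-week course) or 7 − 5 = 2 (five-week course)
- M-TFT at T2: 17 − 6 = 11 or more

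Each week of delay before the first session removes one spare week. With a first session in week 3, a 16-session or six-week course cannot be finished by its visit.

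**Share still in treatment at the visit.** Assumptions, none of them from the documents: one slot per week, each slot missed independently with probability p, and the same p in both arms. Let W be the slots available (visit week minus weeks of delay) and s the slots needed. A patient is unfinished if more than W − s slots are missed:

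P(unfinished) = 1 − BinomialCDF(W − s; W, p), and 100% if W < s.

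Example, 16 sessions, week-1 start, p = 5%: 1 − 0.95^17 − 17 × 0.05 × 0.95^16 = 1 − 0.418 − 0.374 = 0.208.

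| First session | p | S-TFT 16, week 17 | S-TFT 13, week 17 | M-TFT six-week, week 7 | M-TFT five-week, week 7 |
|---|---|---|---|---|---|
| Week 1 | 2% | 4.5% | 0.0% | 0.8% | 0.0% |
| Week 1 | 5% | 20.8% | 0.1% | 4.4% | 0.4% |
| Week 1 | 10% | 51.8% | 2.2% | 15.0% | 2.6% |
| Week 2 | 2% | 27.6% | 0.0% | 11.4% | 0.6% |
| Week 2 | 5% | 56.0% | 0.7% | 26.5% | 3.3% |
| Week 2 | 10% | 81.5% | 6.8% | 46.9% | 11.4% |
| Week 3 | 2% | 100% | 0.3% | 100% | 9.6% |
| Week 3 | 5% | 100% | 3.6% | 100% | 22.6% |
| Week 3 | 10% | 100% | 18.4% | 100% | 41.0% |

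At week 17 the six-week M-TFT share is essentially 0% in every row.

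**Does the direction between arms hold at each arm's own end visit?** Take an assumed 50:50 mix of the two S-TFT formats against six-week M-TFT, at p = 5% and 10%:

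- Week-1 start: (20.8 + 0.1)/2 = 10% v 4%; (51.8 + 2.2)/2 = 27% v 15%. S-TFT is higher.
- Week-2 start: (56.0 + 0.7)/2 = 28% v 26%; (81.5 + 6.8)/2 = 44% v 47%. The sign changes.
- Week-3 start: (100 + 3.6)/2 = 52% v 100%; (100 + 18.4)/2 = 59% v 100%. M-TFT is higher.

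The 16-session share above which S-TFT is the worse arm is (M6 − S13)/(S16 − S13). For a week-1 start this is 4.3/20.7 = 21% (p = 5%) and 12.8/49.6 = 26% (p = 10%). For a week-2 start it is 25.8/55.3 = 47% and 40.1/74.7 = 54%. Against five-week M-TFT courses the 50:50 mix stays higher throughout. The documents give neither the site mix nor the split of M-TFT courses.

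**Primary test.** Nine months is about 39 weeks, so the decision falls 39 − 17 = 22 weeks after T2.

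**The case against.** The best defence is that a common calendar from baseline is a sound design for a trial that expects faster relief under M-TFT: patients still in weekly therapy at week 17 are part of that contrast. The only stated decision test is at 9 months, and no T2 test is announced as a post-treatment comparison. The evaluation section already intends the forms to come after treatment. Visit windows and the handling of late finishers may stand in the full protocol, which is not shown, so their absence from an article is no fault. CSQ-8 appears only in Table 1, without a stated comparison between arms.

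Most of this stands. It confines the point to the visit labels and to the timing of two self-report forms. It does not remove the point, because the article itself anchors the visits to baseline, equates them with the end of treatment and ties the forms to them.

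A reader might infer more: that many spaced patients will be rated as finished while still in treatment, and more often than massed patients. The documents support neither. They give no rate of missed weeks and no start delay. The 13-session format is unfinished less often than six-week M-TFT in every row of the table. Nor do they show that weeks will slip mainly in S-TFT. The Introduction says only: "With less potential for therapy disruption, M-TFT might benefit patients with outside constraints interfering with therapy". That is a conjecture about benefit, and the calculation uses equal rates.

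**Conclusion.** The point holds in limited form. The visit labelled as end of treatment can precede the last session, mainly at sites using "16 weekly 50-minute sessions" and in six-week M-TFT courses. The spare weeks (1, 4, and 1 or 2) follow from the article alone. The shares do not: with a week-1 start and 2% to 10% missed weeks they are about 5% to 52% for 16-session S-TFT, 0% to 2% for 13-session S-TFT and 1% to 15% for six-week M-TFT, and a later start raises them. Which arm is worse at its own end visit depends on site mix, start delay and M-TFT course length, and cannot be settled from the documents.

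At week 17 itself the direction is clear: only S-TFT patients can realistically still be in treatment. The T2 contrast is therefore valid as a comparison at week 17, but not a clean post-treatment comparison. A reader might extend this to the primary conclusion. That does not follow, because the non-inferiority test at 9 months is not affected.

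**What to change.** This is a cheap improvement, not the repair of a fault in the primary analysis.

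1. Keep CAPS-5-R, EQ-5D-5L, MHQoL, TiC-P and the other repeated measures at their fixed weeks.
2. Send the CSQ-8 + VAS and the treatment format evaluation within one fixed window after each patient's actual last session, whether treatment was completed or stopped. Use the same window in both arms.
3. In Table 1 and the text, label T1 and T2 as week 7 and week 17.
4. Record the date of the last session. Report, by arm and session format, the share still in treatment at T1 and T2.
5. Do not present the T2 contrast as post-treatment.

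Cost: a changed trigger for two forms in the data capture system, new visit labels and an amendment. The forms would no longer coincide with a scheduled online visit, so a reminder is needed and response may be slightly lower. Inclusion began in November 2024, so participants before and after the amendment would have different form timing. For that reason, report the date of form completion relative to the last session. For the repeated measures the change affects only labels and reporting.
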